### Design and study setting

We will use a parallel-group, two-arm, cluster randomised controlled trial design to evaluate whether our intervention is superior to the existing treatment (control). We will conduct the study in MSI clinics (formally known as static service delivery centres) across Ethiopia and Vietnam. All clinics in Ethiopia and Vietnam are in urban areas, and typically serve clients with higher incomes than is average for the country. In 2015, 11% of Ethiopian clients and 1% of Vietnamese clients visiting clinics lived below the poverty line of $1.25. Although MSI charges clients for FP services, they have a policy of offering a discount or waiver for clients who cannot pay. Typically, the vast majority of clients self-refer after hearing of the services offered by MSI through social networks.

Clinics are staffed by formally trained clinicians (providers), who are employed and trained by MSI, and the intervention will be delivered by MSI FP providers at the clinic level, with the clinic being the unit of randomisation. A clustered design is necessary because it will not be feasible for clinic providers to switch between delivering the intervention (which involves training) or control treatment to clients. Moreover, this design avoids the risk of contamination between different providers within clinics. In addition to the trial, we will use a structured observational survey to explore how providers are using DCA and counselling clients in the intervention arm. We will also conduct a qualitative study using in-depth interviews with providers and clients to understand their experiences of using and receiving DCA-led FP counselling, respectively, which will also help us understand if and how it can be improved.

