### Participants, recruitment and consent

We will invite all MSI clinics in Ethiopia (24) and Vietnam (11) to participate in the study, via the respective MSI in-country directors. All providers will be invited to participate, and we will seek verbal informed consent from providers for their participation, but only those passing an assessment of their knowledge of the intervention at the end of the intervention training will be eligible to continue to participate.

Eligible participants will be women aged 18–49 years old who present at MSI clinics and receive FP counselling. During the recruitment phase of the trial, we will recruit participants across all participating clinics as they present consecutively for FP counselling, until clinics reach their target sample size. Clients attending MSI clinics for FP counselling will initially be asked, either by the receptionist or by the provider (if there is no receptionist), if they can be contacted by a researcher via telephone in the next 2 days who will ask them some questions about their experience of the study. Those who agree will then be telephoned in the next 2 days by a researcher for an exit interview. The researcher will then seek formal verbal informed consent from the client to conduct the exit interview and provide outcome data for the trial. They will also be asked if they can be contacted again at 4 months for a follow-up interview. Those clients who agree will then be contacted at 4 months after their FP counselling session by a researcher, again via telephone. Again they will first seek formal verbal informed consent for the interview before collecting the 4-month follow-up data. At both the initial and 4-month telephone interviews, clients who agree to be contacted but who do not answer their phone or are otherwise busy will be contacted again twice more over subsequent days, before being recorded as lost to follow-up. For clients lost to follow-up, their anonymous basic demographic data along with their choice of FP method will be collected from their clinic’s routine records (see Section 2.13 on statistical analyses for details of which patients will be included in the analyses). Clients will not receive remuneration for their time.

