### Primary outcome

The primary outcome will be reported LAPM uptake. This is defined as the proportion of switchers and adopters who report choosing a LAPM following FP counselling (rather than a short-acting method). Switchers are clients using any FP method at the time of counselling who then change to any other FP method following counselling. Adopters are clients who are not using any FP method at the time of counselling but who decide to start using any FP method following counselling. LAPM methods include contraceptive implants, IUDs, intrauterine systems and tubal ligation, with all other FP methods considered short-acting methods. This outcome will be calculated from data collected at the initial telephone exit interview, and its accuracy is, therefore, dependent on the accuracy of clients’ responses. This primary outcome (reported LAPM uptake) is already used by MSI as a clinic performance indicator, making it feasible to collect this information. It is also a key indicator of FP practices supporting sustainable development goals 3 and 5.

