### Sample size

Based on logistical considerations, we assume that we can recruit 75 clients per clinic across 35 clinics during the recruitment period. Based on routine MSI clinic data, we estimate that the primary outcome of LAPM uptake in switchers and adopters is currently typically around 40%. We, therefore, estimate that we will have 80% power to detect an absolute increase in LAPM uptake from 40% to 50.5% (judged by trial researchers and MSI FP experts to be a sufficiently small, clinically important difference for these contexts) at a 5% level of statistical significance, assuming a between-cluster coefficient of variation of 0.2 (based on prior MSI routine data), with 18 clinics in the intervention arm and 17 in the control arm, and 75 clients recruited per clinic [20].

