### Statistical analyses

We will use methods suitable for cluster trials with relatively few clusters, analysing cluster-level summary measures (proportions) of all binary outcomes to account for between-cluster variation, and reporting crude and covariate-adjusted results [21]. We first will convert all Likert and numeric scale outcomes into binary scale outcomes. As laid out above, the four-point Likert scale outcomes will be dichotomised by combining the first two categories and then the final two categories. The two 5-point Likert scale outcomes will be dichotomised by combining the first two categories and then the final three categories. The five-point numeric scale outcomes will be dichotomised by combining the first three categories and then the final two categories. For all outcomes, we will first estimate the crude intervention effect as the difference between the mean intervention arm and mean control arm cluster-level outcome proportions (i.e. a risk difference), and we will estimate the 95% confidence intervals and *p* value associated with this effect size estimate using an independent *t*-test.

We will then estimate covariate-adjusted results using a two-stage method [21]. First, using a logistic regression model, we will model the effects of our covariates of interest on the individual-level binary outcomes, while excluding the effect of treatment. We will then use the individual-level model predicted values and the individual-level observed values for each outcome to calculate covariate-adjusted cluster-level difference residuals. Lastly, we will use these values in place of cluster-level summary outcome measures to estimate covariate-adjusted risk differences, and again use *t*-tests to estimate the associated 95% confidence intervals and *p* values. We will adjust outcomes for covariates as shown in Table 1. In addition, using the methods outlined in Hayes & Moulton [21] for analysing cluster-level effect modification, we will assess whether the treatment effect differs for the primary outcome between the following subgroups: Ethiopia vs Vietnam and switchers vs adopters.

**Table 1 Tab1:** Planned covariate adjustment for covariate-adjusted analyses

Outcome	Covariates adjusted for
Primary (LAPM uptake among FP switchers and adopters)	1–8
Proportion of clients recommended a LAPM by their provider	1–8
How well clients felt providers listened to their needs	1–8

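### One method named for cluster-level effect modification covers both subgroup tests, but switcher/adopter status is a client-level modifier; read literally, the test has the right size only if a clinic's two subgroup effects are uncorrelated

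*Protocol article*

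**What the plan says.** All places are in the protocol article.

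- **Statistical analyses** names one approach for the primary outcome's subgroup tests: methods from a cited textbook "for analysing cluster-level effect modification, we will assess whether the treatment effect differs for the primary outcome between the following subgroups: Ethiopia vs Vietnam and", as the second pair, switchers v adopters. No formula for the interaction test is printed.
- **Design and study setting** sets the trial up "with the clinic being the unit of randomisation". Each clinic lies in one country.
- **Primary outcome** defines the other modifier client by client: "Switchers are clients using any FP method at the time of counselling who then change to any other FP method following counselling", while "Adopters are clients who are not using any FP method at the time of counselling" and then start one.
- **Participants, recruitment and consent** does not select by current contraceptive use: "we will recruit participants across all participating clinics as they present consecutively for FP counselling, until clinics reach their target sample size".
- **Sample size** gives 18 v 17 clinics, 75 clients per clinic, 40% v 50.5% uptake and 80% power, "assuming a between-cluster coefficient of variation of 0.2". It states no power or precision for either subgroup test.

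**The concern.** The two modifiers need different error terms. For Ethiopia v Vietnam, each clinic falls in one level, so the clinic summaries in the two levels are independent. For switchers v adopters, consecutive recruitment makes it very likely that nearly every clinic supplies both groups. A clinic's two proportions come from the same staff, the same site and the same range of available methods, so they probably move together. A within-clinic contrast cancels that shared variation. A test that treats the clinic-by-subgroup proportions as independent leaves it in the standard error.

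At stake is one of only two planned subgroup tests of the primary outcome. If the correlation is positive, the test rejects too rarely and its interval is too wide, so a real difference in effect between switchers and adopters is more easily reported as absent. If it is negative, the test rejects too often.

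**Working it through.** **Inputs from Sample size:** n1 = 18, n0 = 17 clinics; m = 75; p0 = 0.40; p1 = 0.505; k = 0.2; 5% level, two-sided (Statistical analyses).

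**Assumptions, not in the article:** switcher share s; fraction of the 75 clients who are switchers or adopters; correlation ρ between a clinic's switcher and adopter effects; a true interaction of 10.5 points for power.

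**Step 1, the plan's own figure.** Clinics per arm:

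c = 1 + (1.96 + 0.842)² × [p0(1−p0)/m + p1(1−p1)/m + k²(p0² + p1²)] / (p1−p0)²

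The bracket is 0.0032 + 0.00333 + 0.0166 = 0.0231. Hence c = 1 + 7.85 × 0.0231/0.01103 = 17.47 per arm, or 35 clinics. With 18 v 17 clinics and a t reference on 33 df, power is 80.2%. The stated 80% reproduces.

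**Step 2, variance of the subgroup contrast.** For an arm with uptake p and subgroup sizes mS and mA:

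- within-clinic difference: 2(kp)²(1−ρ) + p(1−p)(1/mS + 1/mA)
- two proportions taken as independent: 2(kp)² + p(1−p)(1/mS + 1/mA)

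Divide by the number of clinics in the arm, add the arms, and take the root. The paired interval uses t on 33 df (2.035). The unpaired one uses 66 df (1.997), from 70 proportions in four arm-by-subgroup cells.

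**Step 3, even split, all 75 contributing (mS = mA = 37.5).** Unpaired: intervention (0.0204 + 0.0133)/18 and control (0.0128 + 0.0128)/17 give SE 0.0581 and half-width 11.6 points. Paired at ρ = 0.5: (0.0102 + 0.0133)/18 and (0.0064 + 0.0128)/17 give SE 0.0494 and half-width 10.0 points.

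| ρ | Paired half-width (points) | Unpaired half-width (points) | Unpaired/paired | Power paired v unpaired |
|---|---|---|---|---|
| −0.5 | 13.4 | 11.6 | 0.87 | 34% v 43% |
| 0 | 11.8 | 11.6 | 0.98 | 42% v 42% |
| 0.5 | 10.0 | 11.6 | 1.16 | 54% v 41% |
| 0.8 | 8.8 | 11.6 | 1.32 | 65% v 40% |
| 1 | 7.9 | 11.6 | 1.48 | 75% v 39% |

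**Step 4, fewer and less even clients** (70% contributing, 20% switchers: mS = 10.5, mA = 42). At ρ = 0.5 the half-widths are 13.3 paired and 14.4 unpaired, so the interval is 8% wider. At ρ = 1 it is 23% wider. At ρ = −0.5 it is 10% too narrow.

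**Step 5, simulation** (binomial counts, CV 0.2, even split, average effect 5.25 points, 20,000 runs per setting). Half-widths are 11.1 unpaired v 9.7 paired at ρ = 0.5, and 11.1 v 8.5 at ρ = 0.8: about 15% and 30% wider. Power, paired v unpaired, is 57% v 45% at 0.5 and 67% v 44% at 0.8. The unpaired test's false-positive rate is about 2% at 0.5, 1% at 0.8, 5% at zero and 8% at −0.5. Where simulated, the paired test stays at about 5%. At ρ = 0 it gives up about 1 point of power (45% v 46%).

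**The case against.** The strongest reply is that the article never states an unpaired test. Elsewhere in Statistical analyses the term cluster-level describes the level of analysis: summaries, proportions and residuals by clinic. On that usage the phrase could mean effect modification assessed on clinic summaries, and a t-test on within-clinic differences is exactly that. The textbook is not at hand, and the article defers its planned analyses to an SAP that is not shown.

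This stands in part. A reader might infer that the plan certainly ignores the pairing and therefore loses power. The documents do not support that. No formula is printed, no correlation is given, and the presence of both groups in every clinic is very likely but unstated. At zero correlation nothing material is lost, and at negative correlation the error reverses.

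Three further points reduce the size. Clients renewing a satisfactory method (the first pathway under Intervention) are neither switchers nor adopters, so fewer than 75 will contribute. The main inference is covariate-adjusted, which may remove some of the shared clinic variation; the figures above are for crude proportions. And with positive correlation the error is conservative.

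The reply does not remove the point. The article does not leave the method open: it puts one label on two modifiers that need different error terms. An analyst could follow that text literally and run a test of the wrong size.

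**Conclusion.** The point holds in a limited form. The named method suits country and, read literally, does not suit switcher/adopter status. Its test would then be correctly sized only near zero correlation between a clinic's two subgroup effects. The likely direction is a too-wide interval: about 15% at correlation 0.5 and 30% at 0.8 under the even-split, full-contribution assumption, and about 8% at 0.5 under the less favourable one. These sizes rest on assumed correlations, shares and contribution rates.

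A reader might extend the criticism to the main analysis. That is not supported: the t-test on clinic proportions matches the clustered design, and the 80% power reproduces. Nor would pairing make this a well-powered subgroup test. Even paired, power for a 10.5-point interaction is 54% to 57% at correlation 0.5, so a null result would remain inconclusive. The change is worth making because the paired test keeps its size whatever the correlation.

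**What to change.** Keep the method for cluster-level modifiers for Ethiopia v Vietnam only. For switchers v adopters, state that each clinic's switcher-minus-adopter difference will be computed, once from crude proportions and once from the covariate-adjusted residuals. Compare these differences between arms with the same independent t-test, on 33 df if all 35 clinics contribute. Report the difference in risk differences with its 95% confidence interval, and say how clinics with only one subgroup are handled.

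The cost is one or two sentences in the article's analysis section or the SAP, with no new data. If the SAP already specifies the within-clinic contrast, only the article's wording needs aligning. The downsides are small: a clinic with only one subgroup drops out of this contrast, and power falls by about 1 point if the correlation is in fact zero.

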In recognition of these factors, the intervention aims to support the uptake of modern methods through quality client-centred counselling. The intention is to standardise the quality of care in FP counselling to inform clients and empower them to select their preferred method. We hypothesise that DCA will offer a more client-focused counselling process, increasing providers’ consideration of clients’ circumstances and needs, reducing bias in provider recommendations, limiting discussion of all possible FP methods but expanding discussion on client-preferred methods (as ranked by DCA) designed to suit clients’ needs and preferences. This is anticipated to improve users’ counselling experience and increase clients’ readiness to consider and accept a LAPM. Our primary objective is, therefore, to evaluate the effects of DCA on LAPM uptake among clients attending FP counselling at MSI clinics in Ethiopia and Vietnam. We will also explore any effect of the DCA-led client-centred counselling on continuation rates of LAPM uptake, since providers are actively prompted to provide an upfront discussion of the side effects in advance of LAPM uptake compared to traditional counselling. The trial is also supported by a qualitative exploration of providers’ and clients’ experience of DCA, to identify where and how DCA can be improved.

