### Secondary outcomes

The following secondary outcomes use data from initial client exit telephone interviews:Proportion of clients recommended a LAPM by their provider.How well clients felt providers listened to their needs, measured on a four-point Likert scale: (1) listened well, (2) listened quite well, (3) did not listen well or (4) did not listen at all well.The degree to which clients felt the methods recommended by providers were relevant to their needs, measured on a four-point Likert scale: (1) very relevant, (2) a bit relevant, (3) not very relevant or (4) not at all relevant.How well clients felt they understood the potential side effects of their chosen method, measured on a four-point Likert scale: (1) understand very well, (2) understand quite well, (3) do not understand well or (4) do not understand at all well.How clients felt about the amount of information given to them during counselling sessions, measured on a five-point Likert scale: (1) much too little, (2) slightly too little, (3) about right, (4) slightly too much or (5) much too much.How clients felt about the length of their counselling sessions, measured on a five-point Likert scale: (1) much too short, (2) slightly too short, (3) about right, (4) slightly too long or (5) much too long.How clients rated their experience of receiving counselling, measured on a five-point numeric scale where 1 was “bad” and 5 was “good”.

The following secondary outcomes use data from client 4-month telephone interviews:Proportion of adopters or switchers who chose a LAPM following their FP counselling session and reported still using the same method at 4 months.Proportion of adopters or switchers who chose a LAPM following their FP counselling session and who report that they plan to continue using their current method.Proportion of clients who chose any short-acting FP method following their FP counselling and reported still using the same method at 4 months.Proportion of clients who chose any short-acting FP method following their FP counselling and who report that they plan to continue using their current method.How clients rated their overall satisfaction with the FP method they chose following their FP counselling at 4 months, measured on a five-point numeric scale where 1 was “bad” and 5 was “good”.

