How relevant clients felt the method(s) recommended by providers were to their needs	1–8
How well clients felt they understood the potential side effects of their chosen method	1–3, 5–6, 8
How clients felt about the amount of information given to them during counselling sessions	1–8
How clients felt about the length of their counselling sessions	1–8
How clients rated their experience of receiving counselling	1–7
Proportion of adopters or switchers who chose a LAPM following their FP counselling session and reported still using the same method at 4 months	1–9
Proportion of adopters or switchers who chose a LAPM following their FP counselling session and who report that they plan to continue using their current method	1–9
Proportion of clients who chose any short-acting FP method following their FP counselling and reported still using the same method at 4 months	1–9
Proportion of clients who chose any short-acting FP method following their FP counselling and who report that they plan to continue using their current method	1–9
How clients rated their overall satisfaction with the FP method they received following their FP counselling at 4 months	1–8

*FP* family planning, *LAPM* long-acting or permanent method of contraception, *MSI* Marie Stopes International

Covariates: (1) country (Ethiopia or Vietnam), (2) client age, (3) client education level (none, primary, secondary, college or higher), (4) marital status (single or no regular partner, regular partner, married, divorced or separated, refused to say), (5) FP intentions (trying to become pregnant now or within 1 year, aiming to become pregnant within 2+ years, do not want any or anymore children or do not know), (6) current FP usage (currently use LAPM, currently use short-acting or natural method or unsure what method, not currently using any FP method or have never used any FP method), (7) reason for visiting MSI clinic (seeking FP health care, seeking abortion health care or seeking other health care), (8) overall initial rating of FP counselling experience (1–5, where 1 is “bad” and 5 is “good”), (9) overall rating at 4 months of satisfaction with the method received (1–5, where 1 is “bad” and 5 is “good”)

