We will analyse client data based on the original allocation of the clinic that they attended, but we will also conduct sensitivity analyses where we will analyse client data based on how the clinic they attended actually participated in the study (i.e. as either an intervention or control clinic). Prior to the analyses, we will assess the level and pattern of any missingness in outcome or covariate data and investigate the likely causes of missingness. We will conduct complete case analyses of outcomes unless these investigations indicate there is likely to be substantial bias introduced, in which case we will use multilevel multiple imputation methods of analysis [22]. We will make our primary inferences about the statistical significance of the results via formal hypothesis testing. Statistical significance will be at the 5% level based on the (two-sided) *p* values estimated for all outcomes obtained from the covariate-adjusted analyses, as these are likely to have more power and reduced bias (when estimating the treatment effect) than the crude analyses, which will help us to understand how any imbalances in covariates between treatment arms influence the treatment effect [23]. We will evaluate clinical significance based on the effect size estimates and their 95% confidence intervals, with an increase of 10.5 percentage points or more in the primary outcome seen as clinically significant. We will not adjust secondary outcomes for multiple testing. No interim analyses are planned. We will specify our planned analyses in a statistical analysis plan prior to analysis, which will be published with the results.

We will analyse the observation checklist outcomes using survey methods appropriate for the clustered design of the study [24], via the *survey* [25] package in the statistical software R. We will primarily analyse survey checklist outcomes descriptively, either as percentages (categorical outcomes) or as means (continuous outcomes), making inferences about the plausible range of true values for outcomes based on their 95% confidence intervals. We will calculate outcome results from the pooled data and for each country separately, exploring differences in outcomes between countries based on outcome point estimates and 95% confidence intervals.

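### The adjusted analysis that decides significance conditions on the client's rating of the counselling, a post-intervention outcome, so it does not target the total effect of DCA

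*Protocol article*

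**What the plan says.** All of this is in the protocol article.

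- **Covariates.** Under Statistical analyses, Table 1 assigns covariates 1–8 to the primary outcome. Covariate 8 is the "overall initial rating of FP counselling experience" (1–5). It appears in 12 of the 13 rows; the exception is the row for the rating itself (1–7). Covariate 9, the "overall rating at 4 months of satisfaction with the method received", is added in the four rows on 4-month continuation and plans to continue (1–9). It is left out of the 4-month satisfaction row (1–8).
- **Both are outcomes.** Secondary outcomes lists "How clients rated their experience of receiving counselling" from the exit interview and satisfaction with the chosen method at 4 months.
- **Hypothesis.** The Background says of DCA-led counselling: "This is anticipated to improve users’ counselling experience". The same sentence expects clients to become more ready to accept a LAPM. The primary objective is the effect of DCA on LAPM uptake.
- **Method.** Stage 1 is a logistic regression of the individual outcome on the covariates, without a treatment term. Cluster-level difference residuals are then compared between arms by t-test.
- **Basis of inference.** Significance rests on results "obtained from the covariate-adjusted analyses, as these are likely to have more power and reduced bias" than the crude ones. Crude results are also reported.

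**The concern.** Adjustment for characteristics fixed before treatment can sharpen a comparison without changing what it estimates. Adjustment for something measured after treatment, and possibly changed by it, alters the question. The model then asks whether uptake differs between arms among clients who rated their session alike. Any benefit of DCA that comes through a better session is credited to the rating.

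The protocol itself places the rating between DCA and LAPM acceptance. The two reasons it gives for preferring the adjusted analysis, power and reduced bias, are therefore the two properties at risk. At stake are the significance test on the primary outcome and, if the adjusted estimate is the one compared with the 10.5-point threshold, the judgement of clinical significance as well.

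**Working it through.** **1. The plan's own figure.** Inputs from Sample size: p0 = 0.40, p1 = 0.505, m = 75, coefficient of variation k = 0.2, 18 and 17 clinics, 5% level.

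Variance of a clinic proportion: v = p(1−p)/m + k²p².
- v0 = 0.24/75 + 0.04 × 0.16 = 0.0032 + 0.0064 = 0.0096
- v1 = 0.249975/75 + 0.04 × 0.255025 = 0.00333 + 0.01020 = 0.01353

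Clinics per arm: c = 1 + (1.96 + 0.84)² (v0 + v1)/(p1 − p0)² = 1 + 7.849 × 0.02313/0.011025 = 17.47, or 34.9 in total against 35 planned. Power at 18:17 is 80.2% with the one-cluster-per-arm correction and 80.2% with a noncentral t on 33 df. The stated 80% reproduces, but for an analysis without covariate 8.

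**2. When each variable is measured.** Under Participants, recruitment and consent, the exit interview is a telephone call within 2 days after counselling. Covariate 8 is therefore post-intervention in both arms, and it also follows the choice of method. Covariate 9 is collected in the same 4-month interview as the outcomes that it adjusts.

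**3. Illustration of the loss.** The two-stage residual method was simulated with 18 + 17 clinics of 75 clients, uptake of 40% against 50.5%, and 300 trials per scenario. Assumptions, none of them from the protocol:
- a = shift in the latent rating due to DCA, in SD
- b = log-odds of LAPM per SD of rating
- a five-category rating cut from a normal variable
- clinic SD of 0.35 on the logit scale
- rating as the only stage 1 covariate.

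The direct effect was set so that the total effect is always 10.5 points.

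| a | b | effect through rating (points) | crude (points) | adjusted (points) | power crude | power adjusted |
|---|---|---|---|---|---|---|
| 0 | 0.5 | 0.0 | 10.6 | 10.6 | 88% | 89% |
| 0.5 | 0 | 0.0 | 10.5 | 10.0 | 86% | 83% |
| 0.25 | 0.25 | 1.3 | 10.6 | 9.1 | 85% | 76% |
| 0.25 | 0.5 | 2.4 | 10.5 | 7.9 | 86% | 66% |
| 0.5 | 0.25 | 2.4 | 10.8 | 7.9 | 90% | 64% |
| 0.5 | 0.5 | 4.6 | 10.6 | 5.6 | 87% | 38% |

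The loss is close to the part of the effect that runs through the rating. In the last row, 10.6 − 5.6 = 5.0 points against 4.6. The second row isolates the consequence of omitting treatment from stage 1. The rating there has no bearing on uptake, yet it acts as a proxy for arm and absorbs 0.5 points.

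The Monte Carlo standard error of the 38% is √(0.38 × 0.62/300) = 2.8 points, so the low end is best read as 35–38%. Crude power exceeds 80% because a logit SD of 0.35 gives a coefficient of variation of about 0.35 × 0.25/0.505 = 0.17 at 50.5% uptake, below the plan's 0.2.

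**The case against.** **Crude results are planned for every outcome.** An estimate free of this problem will be published beside the adjusted one, which limits the harm. It does not cure the rule, because significance is expressly taken from the adjusted analysis.

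**The analysis plan may change it.** That would answer an omission, but Table 1 fixes the covariates outcome by outcome.

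**The effect of DCA on the rating is a hypothesis.** This stands. A reader might infer that part of the effect is certainly removed, but the protocol only anticipates a better experience, and with a = 0 nothing is lost. The direction is not certain either. The rating follows the choice of method and may reflect that choice or share unmeasured causes with it, so bias another way is possible.

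**Size.** The simulation fits the rating alone, whereas the plan fits covariates 1–8 jointly. It also counts all 75 clients, whereas the primary denominator is switchers and adopters only. It shows a mechanism and does not forecast this trial's loss. Omitting treatment from stage 1 adds to the loss, but only modestly in the one case that isolates it.

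**Readings that go too far:**
- FP intentions and current FP use (covariates 5 and 6) might be called post-treatment because they are asked at the exit interview. The protocol defines switchers and adopters by use when counselled, and describes DCA as identifying fertility intentions, not changing them.
- The exit-interview opinions might be called copies of the rating. The items on amount of information and session length use two-directional scales (too little or short to too much or long), so they do not restate a bad-to-good score.

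**Conclusion.** The point holds. The analysis that decides significance, including for the primary outcome, conditions on a post-intervention variable that is a trial outcome and that the protocol expects DCA to change. It therefore does not estimate the total effect of DCA. This follows from the text and needs no simulation.

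The size is conditional. For rating shifts of 0.25–0.5 SD and slopes of 0.25–0.5 per SD, a true 10.5 points becomes about 9 to 6 points, and power falls from about 80–90% to between 76% and 35–38%. Attenuation is what the protocol's own hypothesis implies, but the documents do not establish it as fact.

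Covariate 9 is a lesser point. It touches only secondary outcomes, and those rows are already restricted by the method chosen after counselling, so removing it would not restore a fully randomised comparison.

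**What to change.** - Delete covariate 8 from every row of Table 1, and covariate 9 from the four continuation and plan-to-continue rows.
- Base inference on covariates 1–7. In the side-effects row, use those listed there without 8 (1–3 and 5–6).
- State that current FP use and FP intentions are taken as status before counselling.
- Label any analysis that includes covariate 8 or 9 as exploratory or mediation analysis.

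The cost is an edit to Table 1, carried into the statistical analysis plan. No new data are needed. The plan is to be specified before analysis, and recruitment was still under way when the article was submitted, so the change can be made before results are known.

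The downside is a small loss of variance reduction. In the simulation with no effect of DCA on the rating, including it gained nothing at b = 0.25, under 1 point of power at b = 0.5 (88.0% to 88.7%), and 3 points at b = 0.75 (86.0% to 89.0%).
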